### Intervention arms

The trial will have 5-arms designed to compare the efficacy of alternative MDCF formulations in repairing the gut microbiota of children with MAM compared to the repair produced by the current kitchen prepared MDCF-2 formulation. All the formulations are fortified with equal amount of vitamins and minerals. Children will be randomly assigned to one of the interventions after enrolment.Arm 1 - Reference control: kitchen-prepared MDCF-2Arm 2 - Individually packaged, pre-measured sachets of MDCF-2 ingredients, combined and reconstituted in the home setting prior to consumptionArm 3 - MDCF-2 shelf-stable foil pouch formulation with green banana powderArm 4 - MDCF shelf-stable foil pouch formulation with sweet potato instead of green bananaArm 5 - Ready-to-use supplementary food (RUSF)

Table 2 provides an overview of the interventions.

**Table 2 Tab2:** Arms and Interventions

	Arms	Intervention
1	Active Comparator: Central kitchen-prepared MDCF-2. Children randomized to this arm will receive 25g of kitchen-prepared version of MDCF-2 twice daily.	Dietary Supplement: Central kitchen-prepared version of MDCF-2. Kitchen-prepared MDCF-2 containing chickpea flour, peanut flour, soybean flour, green banana pulp, sugar, soybean oil and micronutrient mix. This version of MDCF-2 will be freshly prepared in a central kitchen on a daily basis and provided to participants on the same day.
2	Experimental: ‘Jump-start’ version of MDCF-2. Freshly reconstituted MDCF-2 ingredients. Children randomized to this arm will receive individually packaged MDCF-2 ingredients, combined into 21.7 g servings provided twice daily.	Dietary Supplement: Jump-start version of MDCF-2. Freshly reconstituted MDCF-2 ingredients. This version of MDCF-2 is comprised of its individually packaged ingredients. Separate premeasured sachets of chickpea flour, peanut paste, soybean flour, green banana powder, sugar, soybean oil and micronutrient mix will be combined and reconstituted prior to each feeding session.
3	Experimental: MDCF-2 shelf-stable foil pouch prototype with green banana powder. Children randomized to this arm will receive 25g of the shelf-stable foil pouch prototype with green banana powder twice daily.	Dietary Supplement: MDCF-2 shelf-stable foil pouch prototype with green banana powder. This shelf-stable foil pouch prototype of MDCF-2 contains chickpea flour, peanut flour, soybean flour, green banana powder, sugar, soybean oil and micronutrient mix, prepared by an industry partner following the formulation developed at icddr,b.
4	Experimental: MDCF-2 shelf-stable foil pouch prototype with sweet potato. Children randomized to this arm will receive 23.3g of this MDCF prototype with sweet potato twice daily.	Dietary Supplement: MDCF-2 shelf-stable foil pouch prototype with sweet potato. This shelf-stable MDCF prototype contains chickpea flour, peanut flour, soybean flour, sweet potato, sugar, soybean oil and micronutrient mix. This version of MDCF-2 will be prepared by an industry partner following the formulation developed at icddr,b.
5	Experimental: Ready-to-use supplementary food (RUSF). Children randomized to this arm will receive 25g RUSF twice daily.	Dietary Supplement: Ready-to-use supplementary food (RUSF) arm. Locally-produced ready-to-use supplementary food (RUSF) is used as part of a nutritional program to treat moderate acute malnutrition in children over 6 months-of-age. RUSF is eaten directly from the package with no dilution, mixing or cooking. RUSF contains rice, lentil, powdered low-fat milk, soybean oil, sugar, and micronutrient mix.

### Development, delivering & monitoring the interventions

Formulations in arm 1 and arm 2 will be prepared in a kitchen setting. For the rest of the arms, test products will be manufactured in an industrial setting. Each child will receive 250 kcal per day of their assigned formulation. Due to differences in caloric density of the prototypes, the weight per serving of each formulation will be adjusted to ensure equivalent energy provision (Table 2). We have partnered with a large food manufacturer in Bangladesh to develop the shelf-stable, packaged formulations. For this study, we will deliver the industry-made formulations packaged in a trilaminar foil pouch after sterilization. The kitchen-prepared formulations will not be sterilized as these recipes will be delivered immediately after their preparation. A dedicated, BRC- and HACCP-compliant Food Processing Laboratory has been established at the factory site to prepare, package, and sterilize the MDCF and RUSF.

A standardized production procedure is followed throughout the project period to control the quality of the formulations. Raw materials are at first passed through a vigorous quality checking process. The materials are then roasted in a temperature controlled hot air oven followed by a grinding process using a heavy-duty electric grinder to make fine powder/paste as appropriate. To prepare homogenous mixtures, the milled raw materials are shifted to semi-automatic electric mixers to prepare a smooth textured MDCF or RUSF paste. Each step of food preparation, including cleaning, roasting, particle size reduction, and blending, are closely monitored by the study personnel. The paste is then moved to a semi-automatic filler machine in order to fill the trilaminar foil pouch without any direct physical touching by factory personnel. An “Impulse Sealer Machine” is used to achieve airtight sealing of the pouches. Sterilization is performed in a retort machine at 121 °C and 0.208 MPa pressure for a period of 20 minutes. This process ensures a longer contamination-free shelf life while preserving the organoleptic properties of the food. Before distribution to the study site, random samples from each batch will be tested for organoleptic properties and for microbial contamination see Table 3.

**Table 3 Tab3:** Microbiological and Biochemical test

Parameters for Microbiological tests		
Test name	Method	Acceptable limit CFU/gm
Total plate count/Aerobic bacteria/APC	USFDA/BAM	<10,000
Total coliform/*E. coli*	USFDA/BAM	<10
Yeast and Mold Count	USFDA/BAM	<10
*Salmonella*	USFDA/BAM	Nil
*Shigella*	USFDA/BAM/ ISO	Nil
*Bacillus cereus*	USFDA/BAM/ ISO	<10
*Staphylococci*	USFDA/BAM/ ISO	<10
*Enterobacteriaceae*	USFDA/BAM/ ISO	<10
**Parameters for Biochemical tests**		
Test name	Acceptable limit	
pH	6.5-7.5	
Moisture	<2.5% for dry food product	

Acceptability will be assessed at the feeding center by using the 7-point Hedonic scale. A score of 7, corresponds to ‘like extremely’ while a score of 1 corresponds to ‘dislike extremely’ [13].

### Monitoring food consumption and collection of meta-data

Each child will be offered approximately 25 grams of the diet in each feeding session (Table 2). Feeding will take place under the direct supervision of trained study personnel. The intervention diets are pre-weighed. Mothers will be instructed to collect all unconsumed food for weigh-back so that the amount consumed by each child can be calculated. Only water from the mug is allowed to drunk; the amount of water consumed is also measured. The quantity of MDCF or RUSF consumed will be monitored and calculated in every feeding session. Multiple food frequency data and 24 hours dietary recall data will also be collected.

### Outcome measures

Primary Outcome Measure: Equivalence in the response to MDCF-2 and a test MDCF formulation, based on the change in representation of MDCF-2 responsive gut bacterial taxa after 4-weeks of treatment. V4-16S rDNA amplicons and shotgun sequencing datasets will be generated from faecal samples collected from each child in each group prior to, during, and after treatment to determine the abundances of MDCF-2 responsive bacterial taxa. Equivalence will be defined as the absence of a statistically significant difference after 4-weeks of treatment in the representation of faecal bacterial taxa associated with the response to MDCF-2 in participants receiving a test MDCF, compared to the representation of these bacterial taxa in participants after receiving the reference MDCF-2 formulation for 4-weeks. Other pre-specified outcomes changes in the concentrations of faecal protein biomarkers of gut inflammation [myeloperoxidase (Alpco, Salem, New Hampshire), neopterin (GenWay Biotech, San Diego, California), calprotectin (BÜHLMANN fCAL, Schönenbuch, Switzerland), lipocalin-2 (R&D Systems, USA), dual oxidase 2 (MyBioSource, USA)] and protein losing enteropathy [alpha-1-antitrypsin (Biovendo Chandler, North Carolina)]. These proteins will be measured using commercially available ELISA according to the kit manuals. Changes in oxidation-reduction potential and pH of fecal samples will be quantified using a redox meter (PCE-228-R, PCE Instruments, Southampton, United Kingdom) and pH meter (Hanna Instrument, USA), respectively. In addition, changes in the abundances of 7000 circulating plasma proteins that include biomarkers and mediators of various facets of host physiology will be quantified using the SomaScan-aptamer-based proteomics platform (SomaLogic, Boulder CO, USA).

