**Methods:**

A randomized single-blind study will be conducted in 8-12-month-old Bangladeshi children with MAM to compare the efficacy of alternative shelf-stable MDCF prototypes versus the current MDCF-2 formulation that is produced fresh each day. V4-16S rDNA amplicon and shotgun sequencing datasets will be generated from faecal DNA samples collected from each child enrolled in each group prior to, during, and after treatment to determine the abundances of MDCF-2-responsive bacterial taxa. Efficacy will be assessed by quantifying the change in representation of MDCF-2-responsive gut bacterial taxa after 4-weeks of treatment with freshly prepared MDCF-2 compared to their changes in abundance after treatment with the prototype MDCFs. Equivalence will be defined as the absence of a statistically significant difference, after 4-weeks of treatment, in the representation of faecal bacterial taxa associated with the response to MDCF-2 in participants receiving a test MDCF.

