### Sample size

The sample size was informed by the faecal 16S rRNA gene amplicon datasets generated for the proof-of-concept study of 12 to 18-month-old Bangladeshi children with MAM.^11^ In that study, we identified 209 bacterial Amplicon Sequence Variants (ASVs) that were present above 5 counts in at least 5% of the 939 faecal samples analyzed from 118 participants. We calculated 95% confidence intervals (CI; mean ± 1.96 standard error) for the change (delta) in abundance of each of the 209 ASVs between day 0 (pre-intervention) and 4 weeks of intervention for the 59 children in the MDCF-2 treatment group of the POC study. Using a bootstrapping approach with ASV data from 5000 subsets of 20 children from the MDCF-2 group and 5000 subsets of 20 children from the RUSF group, we identified 121 ASVs whose mean changes in abundance for the MDCF-2 subsets fell within the 95% CI of the mean changes for the 59 MDCF-2 participants, but not in children who had received RUSF, with 80% power (“MDCF-2-responsive ASVs”). Therefore, each arm will include a minimum of 20 children who complete the study. Considering potential drop-outs (15%), 23 children will be recruited per arm.

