### Analysis plan

To assess the comparability of microbiota repair elicited by shelf-stable test formulations of MDCF-2 and the reference kitchen prepared formulation, we will sequence PCR amplicons generated from variable region 4 of bacterial 16S rRNA genes present in DNA isolated from faecal samples collected from participants in the different study arms immediately prior to intervention (day 0) and at the end of intervention (day 28). ASV data will be processed using DADA2 [15] and filtered as described [10]. We will calculate 95% confidence intervals of the mean change in abundance of each of the MDCF-2-responsive ASVs identified in this study, between day 0 and day 28, in children who received the reference MDCF-2 formulation, as well as the mean change in abundance for each of these ASVs in participants receiving the test formulations. A test formulation will be considered equivalent to the reference MDCF-2 if >70% of the MDCF-2-responsive ASVs have mean changes in abundance in children consuming a test formulation between day 0 and day 28 that fall within the 95% CI of their mean changes in abundance in the reference MDCF-2 arm. Another embodiment of the analysis of microbial community repair elicited by the reference MDCF-2 and test formulations will involve a comparison of their effects after 28 days of treatment on the abundances of metagenome-assembled genomes (MAGs) identified by shotgun sequencing of the same faecal DNA samples used to produce 16S rDNA amplicons.

Exploratory outcomes will include the effects of the test formulations on features of the plasma and faecal proteomes, including MDCF-2-responsive proteins that are associated with various facets of healthy growth using approaches described in the MDCF-2 POC study [10].

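### The primary outcome defines equivalence as a non-significant difference with no margin, and the Analysis plan gives a different rule without saying which decides

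*Protocol article*

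**What the plan says.** The protocol article gives two rules for one claim.

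- **Non-significance rule.** Outcome measures: "Equivalence will be defined as the absence of a statistically significant difference after 4-weeks of treatment in the representation of faecal bacterial taxa". The Abstract (Methods) repeats it: "Equivalence will be defined as the absence of a statistically significant difference, after 4-weeks of treatment, in the representation of faecal bacterial taxa". Neither place gives a margin or says how results for many taxa combine into one verdict.
- **70% rule.** Analysis plan: "A test formulation will be considered equivalent to the reference MDCF-2 if >70% of the MDCF-2-responsive ASVs have mean changes in abundance" between day 0 and day 28 "that fall within the 95% CI of their mean changes in abundance in the reference MDCF-2 arm". This involves no significance test, and the acceptance region is the reference arm's own confidence interval.

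On size, the Sample size section says: "Therefore, each arm will include a minimum of 20 children who complete the study". The figure of 20 comes from resampling the earlier proof-of-concept (POC) trial. It concerns ASVs whose mean change in subsets of 20 MDCF-2 children fell inside the full MDCF-2 group's interval "but not in children who had received RUSF, with 80% power". That is power to tell MDCF-2 from RUSF. It is not power to conclude that a test food matches MDCF-2.

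**The concern.** Failing to find a difference is a weak result that any small or noisy trial can produce. Under the stated primary definition it becomes the positive finding, so less information makes success more likely. No bound is placed on how different the foods may be.

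The second problem is the unreconciled 70% rule. If the same data can pass one rule and fail the other, and the document does not rank them, the choice can follow the results. The verdict is meant to select a product described as bioequivalent for larger studies on growth outcomes (Discussion), so a false claim could carry a less active product forward.

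**Working it through.** **Inputs from the Protocol article.** 20 completers per arm; 15% drop-out; 23 recruited per arm; 121 responsive ASVs in the POC data; intervals of the form mean ± 1.96 SE, which the article states for the POC data ("We calculated 95% confidence intervals (CI; mean ± 1.96 standard error") and which are assumed here for the trial.

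**Assumptions.** Two-sided 5% tests, normal data with equal SDs, true differences in SD units, and 121 taxa. The Analysis plan refers to responsive ASVs identified in this study, so the actual count may differ.

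**1. The plan's own figure.** 20 × 1.15 = 23, as stated. Dividing instead gives 20 / 0.85 = 23.5, or 24; the gap is immaterial. The bootstrap behind 20 per arm cannot be reproduced because the POC data are not in the document.

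**2. Non-significance rule, one taxon.** The chance of a non-significant result is P(|T| < t crit), with T noncentral t on 2n − 2 df and noncentrality d√(n/2). At n = 20 and d = 0.5 the noncentrality is 0.5 × √10 = 1.58 and t crit is 2.024.

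| True difference 0.5 SD | n=10 | n=20 | n=60 | n=100 |
|---|---|---|---|---|
| P(non-significant) | 82% | 66% | 23% | 6% |

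At n = 20 the figure is 91% for a true 0.2 SD, 31% for 0.8 SD and 13% for 1.0 SD.

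**3. 70% rule, one taxon.** The test-arm mean lies inside the reference interval when the difference in means is below 1.96 s/√n, with s the reference-arm SD. Dividing by s√(2/n), this is P(|T| < 1.96/√2 = 1.386), with T noncentral t on n − 1 df and the same noncentrality.

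- Identical foods, n = 20: 0.82. It falls short of 0.95 because sampling error in the test arm is ignored.
- True 0.5 SD: 0.58 at n = 10, 0.415 at n = 20, 0.09 at n = 60. The acceptance region widens as n falls; its half-width is 1.96/√10 = 0.62 SD at n = 10 and 1.96/√20 = 0.44 SD at n = 20.

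**4. The rules compared at n = 20.** For one taxon, the reference interval is breached beyond an observed difference of about 0.44 SD, but significance needs 2.024 × √(2/20) = 0.64 SD. At a true 0.5 SD the taxon is non-significant in 66% of trials and inside the interval in 41.5%.

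Across 121 taxa, 0.70 × 121 = 84.7. At least 85 must therefore lie inside, and 36 may lie outside. With identical foods and independent taxa:

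- no significant taxon at unadjusted 5%: 0.95^121 = 0.002, or 0.2%, with 0.05 × 121 ≈ 6 significant taxa expected;
- 70% rule: P(Binomial(121, 0.82) ≥ 85) > 99%.

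Simulation with a common correlation of 0.5 between taxa gives 18% and 83%. For a single taxon the non-significance rule is the looser one; required of every taxon without adjustment, it is far the stricter.

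**5. What a margin would require.** Two one-sided tests (TOST) at 5% each, true difference 0 and 80% power need n = 2(1.645 + 1.282)²/Δ² per arm for one endpoint.

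| Margin Δ (SD) | 0.3 | 0.5 | 0.8 | 1.0 |
|---|---|---|---|---|
| n per arm | 191 | 69 | 27 | 18 |
| Power at n=20 | 0% | 0% | 62% | 87% |

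Inverting at n = 20: Δ = (1.645 + 1.282) × √(2/20) = 0.93 SD.

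**The case against.** The best defence is that the Analysis plan holds the only operational rule, with time points, an interval and a threshold. The sample-size bootstrap rests on the same idea of a mean change inside an interval, so the non-significance sentences may be a loose summary. The 70% rule also discriminates: in simulation it passes in 83% to over 99% of trials with identical foods, and in 0 to 19% when every ASV shifts by 0.5 SD (correlation 0.5 down to 0 in the first range, 0 up to 0.5 in the second). This stands as far as it goes. But the primary outcome is still defined by non-significance, no text subordinates that definition, and the 70% rule has the weaknesses shown in step 3.

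Four stronger readings are tempting and are not supported.

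- **Multiplicity correction makes equivalence almost automatic.** Bonferroni power for one taxon at 0.8 SD is only 11%, but a verdict over the whole set needs every taxon to be non-significant. If all 121 differ by 0.8 SD and are independent, that chance is (1 − 0.114)^121 ≈ 4 × 10⁻⁷. With all shifted by 0.5 SD it is 10 to 58% over correlations of 0 to 0.5.
- **The sections analyse different quantities.** The equivalence sentences speak of representation after 4 weeks, but the Abstract and Outcome measures both also name change in representation. This is loose wording to be aligned.
- **This is the trial's only confirmatory claim.** The article calls the study pre-POC, and its primary goal includes acceptability.
- **Twenty children can never show equivalence.** They can, for a margin near 0.93 SD. The failure lies in the non-significance definition.

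**Conclusion.** The primary definition is wrong as written. With 20 per arm it would label a taxon with a true 0.5 SD difference as not different in 66% of trials, and the figure rises as the sample shrinks. The conflict with the Analysis plan is also real: no text says which rule decides, and identical foods could pass one rule in 0.2% of trials and the other in over 99%. An unseen analysis plan could supply test details, but it would not remove a definition and a contradiction already in the published text.

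The logical defect does not depend on any number. The sizes rest on assumed effect sizes, a two-sided 5% level, normal data and 121 taxa; the 0.2% and 99% figures also assume independent taxa and narrow to 18% and 83% at correlation 0.5. Adopting the 70% rule alone would end the contradiction but would not make the verdict a demonstration of equivalence.

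**What to change.** 1. Delete the non-significance definition from the Abstract and Outcome measures, and word both in terms of change from day 0 to day 28.
2. Name one primary equivalence rule: the confidence interval of the test-minus-reference difference in that change must lie inside a margin fixed before the outcome data are analysed. The POC data in hand can inform the margin.
3. State how taxa are combined. A weighted composite of responsive ASVs, or a margin set at half the POC difference between MDCF-2 and RUSF, are options and not requirements. POC weights would come from children aged 12 to 18 months, whereas this trial enrols at 8 to 12 months.
4. Make the MAG analysis supportive.
5. If the margin is not met, report that no difference was detected, or describe similarity on the 70% criterion, without calling the food equivalent.

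The cost is wording plus one justified margin. The real price is a harder claim: with 20 per arm, 80% power exists only for a margin near 0.93 SD, and a 0.5 SD margin would need 69 per arm. If no margin that wide can be defended, the trial should be presented as a descriptive comparison for choosing a formulation.

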### Sample size

The sample size was informed by the faecal 16S rRNA gene amplicon datasets generated for the proof-of-concept study of 12 to 18-month-old Bangladeshi children with MAM.^11^ In that study, we identified 209 bacterial Amplicon Sequence Variants (ASVs) that were present above 5 counts in at least 5% of the 939 faecal samples analyzed from 118 participants. We calculated 95% confidence intervals (CI; mean ± 1.96 standard error) for the change (delta) in abundance of each of the 209 ASVs between day 0 (pre-intervention) and 4 weeks of intervention for the 59 children in the MDCF-2 treatment group of the POC study. Using a bootstrapping approach with ASV data from 5000 subsets of 20 children from the MDCF-2 group and 5000 subsets of 20 children from the RUSF group, we identified 121 ASVs whose mean changes in abundance for the MDCF-2 subsets fell within the 95% CI of the mean changes for the 59 MDCF-2 participants, but not in children who had received RUSF, with 80% power (“MDCF-2-responsive ASVs”). Therefore, each arm will include a minimum of 20 children who complete the study. Considering potential drop-outs (15%), 23 children will be recruited per arm.

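### The screen for MDCF-2-responsive ASVs requires a difference from RUSF but no change on MDCF-2, so the >70% equivalence rule may partly reward absence of change

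*Protocol article*

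**What the plan says.** The Sample size section of the protocol article starts from 209 ASVs in the proof-of-concept (POC) study. For each ASV it forms a 95% CI (mean ± 1.96 SE) of the change from day 0 to 4 weeks "for the 59 children in the MDCF-2 treatment group of the POC study". It then draws "5000 subsets of 20 children from the MDCF-2 group and 5000 subsets of 20 children from the RUSF group". An ASV is labelled MDCF-2-responsive if two conditions hold:

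- its "mean changes in abundance for the MDCF-2 subsets fell within the 95% CI of the mean changes" for those 59 children;
- the same is not true of RUSF: "but not in children who had received RUSF, with 80% power".

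This yields 121 ASVs and a target of 20 completers per arm.

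The Analysis plan uses the label as the denominator of the primary decision. A test food is "considered equivalent to the reference MDCF-2 if >70% of the MDCF-2-responsive ASVs have mean changes" that lie inside the reference arm's 95% CI. Neither section requires the change on MDCF-2 to differ from zero or to have a stated direction. Neither requires the reference or test arm to show any change from day 0.

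**The concern.** The question under Goal and objectives is whether the new formulations repair the microbiota as fresh MDCF-2 does. A list meant to measure repair should hold taxa that MDCF-2 moves. The first condition cannot ensure this, because it asks only whether part of a sample resembles the whole. The second asks whether RUSF differs from MDCF-2, and that difference can arise because MDCF-2 moved the taxon, because RUSF did, or both.

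A taxon that only RUSF moved still enters the count. On that taxon a food that does nothing agrees with MDCF-2 as often as a perfect copy would. If enough of the list is of this kind, a product that has lost its activity could be called equivalent in repair and carried into the larger studies that the Discussion foresees.

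**Working it through.** **The plan's own figures.** The 23 recruited per arm follows from 20 × 1.15 = 23 and is not at issue here (20/0.85 = 23.5 would round up to 24). The 121 cannot be reproduced, because no ASV means or SDs are given.

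**Inputs.** Sample size section: 209 ASVs, 59 MDCF-2 children, subsets of 20, CI of mean ± 1.96 SE, 80%, 20 completers per arm. Analysis plan: >70%, reference-arm 95% CI. Assumptions: changes in SD units, normal means, equal SDs, independent ASVs, and 59 RUSF children (118 participants less 59).

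**Step 1: the MDCF-2 condition.**
- CI half-width: 1.96/√59 = 0.255 SD.
- SE of a subset of 20, without replacement: √[(1/20)(1 − 20/59)] = 0.182; P(|Z| < 0.255/0.182) = 0.84.
- With replacement: 1/√20 = 0.224; P = 0.75.

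The true change cancels, so the result is the same for a flat ASV and a strong responder.

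**Step 2: the RUSF condition.** With observed arm difference d, P(RUSF subset inside) = Φ((0.255 − d)/s) − Φ((−0.255 − d)/s), where s is the subset SE. The article does not settle how the 80% applies to this condition.
- Strict reading (inside in at most 20% of draws): |d| must be at least 0.41 SD. If the foods do not differ, d has SD √(2/59) = 0.184, so 2.7% of ASVs pass, about 6 of 209.
- Lenient reading (inside in under 80%): |d| above 0.08 SD suffices. About 66.5% pass with no true difference, about 139 of 209.

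On either reading the condition concerns the difference between foods only.

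**Step 3: the equivalence rule at 20 per arm.** The reference CI half-width is 1.96/√20 = 0.438 SD. The difference of two arm means has SE √(2/20) = 0.316. An inert food falls inside with probability Φ((0.438 − δ)/0.316) − Φ((−0.438 − δ)/0.316), where δ is the true change on MDCF-2.

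| δ (SD) | Inert food inside |
|---|---|
| 0 | 83% |
| 0.25 | 71% |
| 0.30 | 66% |
| 0.41 | 53% |
| 0.5 | 42% |
| 0.6 | 30% |
| 1.0 | 4% |

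The figure falls to 70% at δ = 0.26 SD. A truly identical food scores 83% at every δ. Passing needs at least 85 of 121; at 83.4% per ASV that is exceeded with probability above 0.999.

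**Step 4: flat share at which an inert food reaches 70% in expectation.** Share = (0.70 − p_δ)/(0.834 − p_δ).
- Others at 0.41 SD: (0.70 − 0.532)/(0.834 − 0.532) = 56%, about 67 of 121.
- Others at 0.6 SD: (0.70 − 0.304)/(0.834 − 0.304) = 75%, about 90 of 121.
- Others at 1 SD: 83%; with SDs estimated from the samples (simulated match rates 0.818 and 0.040), 85%.

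**Step 5: strict screen followed by the trial, simulated with 121 of 209 ASVs truly differing between foods.**

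| What moves | Mean inert score | Inert food passes |
|---|---|---|
| All 121 on RUSF only, 0.6 SD | 84% | about 100% |
| Two thirds on RUSF, one third on MDCF-2, 0.6 SD | 66% | 17% |
| Opposite directions, 0.3 SD each | 66% | 20% |
| Half and half, 0.6 SD | 58% | 0.2% |
| All 121 on MDCF-2 only, 0.6 SD | 31% | 0% |

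**The case against.** **The RUSF condition is a real filter.** On the strict reading only about 6 of 209 null ASVs would pass, so a list of 121 would mostly reflect true contrasts between foods, and a RUSF-like food would usually fail. This stands. A reader might infer from the lenient reading that the 121 could be pure noise. The article does not support that: noise alone would give about 139, true differences would only add to it, and 121 lies about 2.6 SD below it (SD √(209 × 0.665 × 0.335) = 6.8, independent ASVs).

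**The MDCF-2 condition is not automatic at 80%.** The article says bootstrapping. With replacement, a typical ASV is inside in only 75% of draws and would miss an 80% criterion. This stands too, and the exact screen cannot be recovered from the article. Either way, the condition does not depend on the size of the change.

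**The Background points to movement on MDCF-2.** It reports that target taxa rose in the POC study and that standard interventions do not repair immaturity. That makes a mostly flat list less likely, but it gives no count for the 121.

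**A taxon that MDCF-2 holds steady and RUSF shifts is a fair bioequivalence target.** It is, for telling a test food from RUSF. It cannot tell MDCF-2 from no effect, which is what a claim of repair needs.

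**No test arm is inert.** Arms 2-4 are close reformulations, and this is a selection step before larger studies. True, but whether activity survives the change of formulation is what the trial asks, and the inert food marks the limiting case.

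**Conclusion.** The definition is deficient as written: it selects ASVs that differ between MDCF-2 and RUSF and labels them responsive to MDCF-2. ASVs that are flat on MDCF-2 can enter the >70% denominator, where an inert food and an identical food both match about 83% of the time.

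The tempting stronger conclusion, that the rule will pass a food that repairs nothing, is not supported. It needs a majority of the list to be flat: about 56-75% if the rest move 0.41-0.6 SD, and up to 85% if they move 1 SD. The article does not report that share, and if most listed ASVs truly move more than about 0.26 SD on MDCF-2, an inert food is expected to fail.

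The Analysis plan's reference to ASVs identified in this study also leaves open whether the 121 or a new list is used; no requirement of change is stated for either. The figures rest on equal SDs, normal means and independent ASVs; correlation between ASVs would make the pass share more variable. Because the list defines the primary decision, the point should be settled before the new sequence data are linked to arm.

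**What to change.** 1. Re-derive the list from the POC data. Require the 95% CI of the MDCF-2 mean change to exclude zero, with its direction recorded, and an MDCF-2 minus RUSF difference in change that is significant under false-discovery-rate control. Report how many of the 121 survive.
2. Freeze the list before new sequence data are linked to arm, and state in the Analysis plan that it is the denominator of the >70% rule.
3. Require the reference arm to reproduce the change in the expected direction before equivalence is judged. Step 1 alone is borderline: a CI excluding zero at n = 59 means an observed change above 0.255 SD, and at a true change of that size an inert food still matches about 70% of the time at 20 per arm. The form of this requirement should be fixed in advance, since a CI excluding zero per ASV at n = 20 would demand 0.438 SD.
4. Report the RUSF arm's score on the same >70% rule, as a check that the rule discriminates.

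The cost is a re-analysis of data already held, with no added children, visits or samples. The list will probably be shorter than 121, so the percentage will rest on fewer ASVs.
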